### 2.2. Selection Criteria

Subjects included in the study:Boys and girls aged 13–17 years,Having obesity, defined as an age- and sex-specific BMI in the 95th percentile or greater (1), or great overweight (age- and sex-specific BMI in the ≥90th to <95th percentile),If they and their parents (or holders of parental responsibility over the child) provide written informed consent (signed by parents and by the adolescent), andHaving easily access to internet (e.g., via mobile phone, tablet, pc).

Exclusion criteria are:Having diabetes and other metabolic, endocrine, and chronic disorders,Intake of antibiotics, drug, probiotics, or nutritional supplements in the last month,Prescribed medicine to control hypertension, inflammation, or dyslipidaemia,Following a prescribed diet for any reason, including weight loss, in the last 3 months,Following a religion-restricted diet, andHaving allergies or food intolerances to nuts, pomegranate, bread, and/or chickpeas.

All volunteers will be examined by physician to assess whether they meet the conditions for inclusion. For this purpose, a medical interview, a physical examination, and laboratory tests will be performed.

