### 2.7. Outcomes

The primary outcome is the BMI z-score, which is a standardized measure of BMI based on specific age and sex [50,51]. The effectiveness of the intervention will be evaluated by comparing the BMI z-score between the control (low-fat diet) and intervention (MD) groups.

The secondary outcomes are:MD adherence, using the KidMed questionnaire [19]Physical activity, using Physical Activity Questionnaire for Adolescents (PAQ-A) [52]Dietary intake and habits:
○3-day dietary records [53]○Food frequency questionnaire (FFQ) of the Helena study [53]
Nutritional knowledge, using the NK Helena questionnaire [54]Quality of life, using the kidscreen-27 Index [55]Sociodemographic data, using the Health Behavior in School Age Children (HBSC) socio-demographic questionnaire [56]Anthropometric data: weight, height, BMI (weight/height^2^), body composition using bioimpedance, waist circumference (WC), and waist–hip ratio (WHR)Blood pressureBiochemical variables, gut microbiota composition, and metabolomics in urine, blood, and feces

All outcomes are presented and summarized in Table 2.

The questionnaires will be used to collect data on the habits and knowledge of the participants in different visits. These data will be collected through the app and then combined with anthropometric and food intake data to assess possible associations among these variables.

At visit (V)1, V2, V3, and V4, the subjects will attend the partner center in over-night fasting conditions to evaluate anthropometric parameters, dietary intake, physical activity, and blood pressure. At V1 and V3, feces, blood, and morning urine will be collected to perform the analyses of microbiota and gut-derived metabolites; food intake biomarkers and phenolic metabolites; circulating levels of glucose and blood lipid profile, biomarkers of insulin resistance, adipose tissue function, inflammation, oxidative stress, and cardiovascular risk, and advanced glycation end products (AGEs). In addition, the lipid profile of the erythrocyte membrane will be assessed at V1 and V3. Data collected at V4 will be used to investigate if the intervention will have changed medium-term dietary habits, having a medium-term impact also on blood pressure and anthropometric parameters. Additionally, for female adolescents, information about their menstrual cycle will be recorded in each visit. Table 3 shows the schedule of each visit, which will follow the same timeline for each enrollment center.

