### 2.8. Sample Size

According to the sample size calculations based on differences in BMI z-score (primary outcome) between groups (0.2 difference with 80% power; two-tailed α: 0.05; standard deviation: 0.5; dropout rate: 20%), a total of 240 volunteers from three Mediterranean countries (Spanish, Portugal and Italy) will be recruited for this study (80 participants per country) after obtaining the approval of the Ethics Committees of each recruiting center and the written informed consent from parents and from subjects.

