### 2.9. Statistical Analyses

#### 2.9.1. Univariate Data Analysis

Data will be expressed as mean ± standard deviation (SD). Grubbs’ test will be used to detect outliers, which will be discarded before subsequent analyses. The normality of variables will be assessed by the Kolmogorov–Smirnov test. Non-parametric variables will be log transformed. Differences in baseline characteristics between subject groups will be analyzed by analysis of covariance (ANCOVA), in which dietary intervention group assignment (G) will be used as a fixed factor and the variables age and sex will be included as covariates. Analyses will be made by intention-to-treat. An ANCOVA model will be used to analyze the data at the end point. The anthropometric and biochemical parameters (changes from baseline) will be used as dependent variables, dietary intervention (MD; low-fat diet) will be included as fixed factor, and the variables age and sex, as well as baseline values, will be included as covariates. Within each group (MD and low-fat diet), changes from baseline will also be analyzed at the end point by a paired *t* test. Within each group (MD and low-fat diet), changes from baseline will also be analyzed considering the different time points using a general linear model for repeated measures. All statistical analyses will be performed with SPSS Statistics (SPSS, Inc., Chicago, IL, USA), setting the level of statistical significance at bilateral 5%. For metagenomics analysis, the non-parametric Mann–Whitney U test will be performed to elucidate pairwise differences on bacteria relative abundance among dietary groups. The Benjamini–Hochberg method will be used to adjust P values for multiple testing considering a 5% false discovery rate. Statistical analyses will be conducted with open-access STAMP software.

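### A normality test on each variable, not on model residuals, decides which outcomes are logged; the rule does not exempt the primary BMI z-score and leaves the order of logging and differencing open

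*Protocol article*

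**What the plan says.** Section 2.9.1 of the protocol article sets out data preparation before any model. After outlier removal it says "The normality of variables will be assessed by the Kolmogorov–Smirnov test", followed by "Non-parametric variables will be log transformed". Next comes the comparison of baseline characteristics, and then the endpoint ANCOVA: "The anthropometric and biochemical parameters (changes from baseline) will be used as dependent variables", with diet as fixed factor, and "the variables age and sex, as well as baseline values, will be included as covariates".

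Section 2.7 names the endpoint: "The primary outcome is the BMI z-score, which is a standardized measure of BMI based on specific age and sex". Section 2.2 admits adolescents with obesity (95th percentile or above) or "great overweight (age- and sex-specific BMI in the ≥90th to <95th percentile", so entry is cut at the 90th percentile. Section 2.8 sizes the trial on a BMI z-score difference of 0.2 with SD 0.5, 80% power, two-sided 5% and 20% dropout, giving 240 in total.

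**The concern.** Three things are left badly fixed by a rule that the article does state.

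- **Wrong object.** The validity of an ANCOVA rests on its residuals given diet, baseline, age and sex. A marginal test on the variable can fail when the residuals are fine, and pass when they are not.
- **No exemption.** Taken as written, the rule covers BMI z-score. That variable already sits on a standardised scale, its baseline is truncated by design, and the sample size is stated on its raw scale.
- **Order and scale.** A change score and a log rule stand side by side without saying which comes first, or whether the baseline covariate is logged too.

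At stake is whether the scale of the primary comparison, and of each biomarker comparison, is known before the data are seen.

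**Working it through.** **1. The plan's own figure.** Inputs from section 2.8: difference 0.2, SD 0.5, two-sided 5%, 80% power.

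n per arm = 2 × (0.5 × (1.960 + 0.842) / 0.2)² = 98.1, so 99 per arm and 198 evaluable. Multiplying by 1.2 gives 238. Dividing by 0.8 gives 248, or 246 if the unrounded n is used. The stated 240 is close to these. With 20% loss, 120 per arm leaves 96, and power is 79%. All of this is on the raw z-score scale.

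**2. Biomarkers, ordinary reading.** Log the visit values, then difference. With log(V1) as covariate:

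log(V3) − log(V1) = a + b·diet + c·log(V1) + … is the same model as log(V3) = a + b·diet + (c + 1)·log(V1) + …

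Only the baseline slope moves, by 1. The diet coefficient, its standard error and its P value are identical. Every strictly positive variable has a defined change whether it rises or falls.

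**3. Biomarkers, if the change itself were logged.** The log does not exist for a change of zero or less. With normal changes, the share lost is Φ(−mean/SD): 50% at mean 0, 58% at −0.2 SD, 66% at −0.4 SD and 79% at −0.8 SD (assumed means). In a simulated skewed biomarker (96 per arm, log-SD 0.7, correlation 0.6, true ratio 0.80, all assumed), 57% of participants are lost and power is about 15%, against 78% for log(V3) on log(V1). These figures belong to this reading only.

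**4. Could BMI z-score fail the test?** The 90th percentile is z = 1.28, if percentile and z-score use the same reference (assumption). In simulated samples of baseline z-scores cut there, Kolmogorov–Smirnov with the Lilliefors correction rejected normality in 13% to 100% of trials, depending on the assumed underlying distribution. Without the correction, rejection ranged from under 1% to 100%. A further check found that rejection falls to about the nominal 5% when the assumed distribution sits well above the cut (mean 2.5, SD 0.5). Failure is plausible, not certain.

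**5. What would logging it do?** A given absolute fall no longer counts equally. From z = 1.28, a fall of 0.2 gives ln(1.08/1.28) = −0.17. From an assumed z = 2.5 it gives ln(2.3/2.5) = −0.08. The effect being tested is no longer the raw difference of section 2.8.

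Simulated power falls from about 78% to 70%. A repeat with 96 per arm, a true difference of 0.2, residual SD 0.5 and six assumed baseline distributions cut at 1.28 gave 78% to 80% for raw change on raw baseline, and 69% to 73% for change in log z on log baseline.

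**The case against.** A reader might infer that the plan prescribes logging the change score, so that everyone whose value falls is dropped, the arms are compared only among those who rose, and intention-to-treat is breached. The documents do not support this. The rule concerns variables, not changes. It stands in a preparation sequence ahead of all models, and it also serves the baseline comparison, where no change score exists. Logging measured values and then differencing is the ordinary reading, and a difference of logged values is still a change from baseline in the transformed variable. By step 2, that analysis is already equivalent to the one recommended here, provided the baseline covariate is logged too. The 57% loss and 15% power therefore cannot be charged to the plan.

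It can also be said that residual checks and lists of skewed markers are details for an analysis plan that is not shown, and that no sensible analyst would log a z-score. The first part would stand if the article were silent, but it states a general rule with a named test on a named object. The second part is probably true in practice, but the written rule does not say so. What stands is that the consequences are modest.

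**Conclusion.** The point holds as a minor one. The biomarker analysis is valid on the ordinary reading; what it lacks is a clause on the order of operations and the scale of the baseline covariate. The firmer defect is that a data-driven test on the wrong object sets the analysis scale without exempting the primary endpoint. If it led to BMI z-score being logged, the analysis would depart from the 0.2 difference and SD 0.5 of the sample size, and power would fall by about 8 points (78% to 70%).

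This rests on BMI z-score falling under the anthropometric parameters to which the rule and the ANCOVA apply, on percentile and z-score sharing one reference, and on assumed baseline distributions. The article gives none of these. The sample size of 240 is not affected.

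**What to change.** Replace the transformation sentences in section 2.9.1 with a rule fixed in advance:

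- BMI z-score is analysed untransformed.
- For biomarkers listed in advance as skewed, visit values are logged. The model is log(V3) on diet with log(V1), age and sex as covariates, reported as the adjusted ratio of geometric means with its 95% confidence interval.
- Any other transformation is judged from the model residuals, not from a Kolmogorov–Smirnov test on the variable.

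This costs a few sentences, with no new data and no change in sample size. The downside is that results for the listed biomarkers read as ratios rather than absolute changes.

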## 2. Materials and Methods

### 2.1. Study Design and Setting

The overall design of the study is represented in Figure 1. The MED4Youth study is a multicenter single-blinded randomized controlled clinical trial with obese and overweight adolescents (13–17 y) from Italy, Portugal, and Spain, in which an MD-based intervention will be compared to a traditional low-fat diet intervention. The three centers involved in the study obtained the approval of the Ethics Committee of each institution: (1) Eurecat (study coordinator): Institut d’Investigació Sanitària Pere i Virgili (Ref. CEIM: 210/2020); (2) UNIPR: Area Vasta Emilia Nord (AVEN) Ethical Committee (pre-approval Ref. Prot. 28638); (3) UC: Ethics Committee of Centro Hospitalar e Universitário de Coimbra and Portuguese National Data Protection Commission (Ref. CHUC-197-20). MED4Youth study was registered at ClinicalTrials.gov (NCT04719052). The protocol conformed to the Helsinki Declaration and Good Clinical Practice guides of the International Conference of Harmonization. This study followed the CONSORT criteria.

According to the sample size calculations, a total of 240 volunteers from Italy, Portugal, and Spain will be recruited for this study (80 participants per country).

The Spanish subjects will be recruited by Eurecat in the province of Tarragona, the Portuguese subjects will be recruited by the Hospital Pediátrico de Coimbra, and the Italian subjects will be recruited by the Pediatric Clinic of the Maternal and Child Department of the Parma University Hospital. The 80 individuals recruited in each country will be randomly assigned to either a MD group (n = 120, n = 40 per country), which will be instructed to follow an MD that will incorporate sourdough bread, hummus, pomegranate, and mixed nuts, or a Control group (n = 120, n = 40 per country), which will be assigned to a standard low-fat diet. The intervention duration is 4 months for each participant, including 3 visits. A follow-up visit after 4 months from the end of the intervention will be carried out.

The randomization code will be computer-generated using software (Geoffrey C. Urbaniak and Scott Plous, Lancaster, PA, USA). Furthermore, the unit responsible for the randomization will be separate from the study researchers.

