### 2.3. Dietary Interventions

Both diets (MD and low-fat diet) will be implemented by dietitians/nutritionists from each center. First of all, the total energy requirements of adolescents will be calculated by using the Molnar equation [41], and the level of physical activity will be obtained from the validated Physical Activity Questionnaire for Adolescents (PAQ-A). Afterwards, a caloric restriction of 20% will be applied to design a personalized diet for each obese individual (BMI ≥95th percentile) [42], while caloric restriction will be carefully evaluated for each individual with great overweight (BMI ≥90 to <95th percentile). For ethical issues, adolescents will not be conscious about caloric restriction of their diet, but only about dietary recommendations to follow the specific diet. In addition to the volunteer’s energy requirements, diets will take into account their food preferences and culture.

A weekly meal general plan, including portion sizes and a list of food equivalents will be provided to participants in both groups, so they could adapt and personalize their menus. The dietary prescription will be also easily accessible by both adolescents and their parents through an educational web-application developed by UNIPR partner. In addition, parents will be provided with a daily recipe to facilitate the adherence to the dietary prescription as well as to increase their culinary skills and the engagement in the project. Moreover, in each country, some recipes will be traditional of another country, i.e., a Spanish recipe in Italy or an Italian plate in Portugal.

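### Allocation is balanced within country but the end-point ANCOVA omits country; if country predicts change, the test is conservative and some power is given up

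*Protocol article*

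**What the plan says.** Section 2.1 (Study Design and Setting) sets the allocation country by country: "The 80 individuals recruited in each country will be randomly assigned to either a MD group (n = 120, n = 40 per country"), against "a Control group (n = 120, n = 40 per country), which will be assigned to a standard low-fat diet". That is a 1:1 split inside each country. The section does not use the words stratified or blocked.

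Section 2.9.1 (Univariate Data Analysis) lists the terms of the end-point model, in which change from baseline is the dependent variable. For the factor it says "dietary intervention (MD; low-fat diet) will be included as fixed factor"; for the covariates, "and the variables age and sex, as well as baseline values, will be included as covariates". Neither country nor centre appears there or elsewhere in section 2.9.

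Section 2.7 (Outcomes) states that "The primary outcome is the BMI z-score". Section 2.8 (Sample Size) treats the trial as a plain two-group comparison: "0.2 difference with 80% power; two-tailed α: 0.05; standard deviation: 0.5; dropout rate: 20"%. It does not say whether the SD of 0.5 is taken within a country or across all three.

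**The concern.** When the arms are balanced within country, a difference in mean response between countries affects both arms equally and cancels from the diet contrast. A model without a country term still counts that difference as residual noise. The reported standard error then describes a less precise experiment than the one performed: intervals are too wide, and the real rejection rate under the null falls below the stated 5%.

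Country could plausibly matter. Recruitment runs through a research institution in one country and hospital paediatric services in the other two (section 2.1). Each centre's own dietitians deliver the diets, and "diets will take into account their food preferences and culture" (section 2.3). Meanwhile the model carries age and sex, for which the BMI z-score is already standardised.

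At stake is precision, for the primary outcome and for the other anthropometric and biochemical outcomes analysed with the same model. The validity of the test is not at stake.

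**Working it through.** **Inputs from the article:** difference 0.2, SD 0.5, two-sided alpha 0.05, power 80%, dropout 20%, N = 240, allocation 40:40 in each of three countries.

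**Input not in the article:** ρ, the share of outcome variance lying between countries after age, sex and baseline. It is varied below.

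**Reproducing the planned size.** A two-sample t-test with standardised effect 0.2/0.5 = 0.4 needs 100 per arm, 200 in total. 200 × 1.2 = 240, the stated figure. With 20% dropout, 240 × 0.8 = 192 remain, or 96 per arm (32 per arm per country if losses are even). Power at 96 per arm is 79.1% (normal approximation).

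**Formulas**, for n = 96 per arm and exact balance within country:

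- Standard error reported without country: SD_total × √(2/n)
- True standard error, and the one reported with country: SD_total × √(1−ρ) × √(2/n)
- Ratio of reported to true: 1/√(1−ρ)
- Actual type I error without country: 2 × [1 − Φ(1.96 × ratio)]
- Power without country: Φ[(0.2 − 1.96 × SE_reported)/SE_true]
- Power with country: Φ[0.2/SE_true − 1.96]

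Example, ρ = 0.10 with 0.5 as total SD: reported SE = 0.5 × √(2/96) = 0.0722; true SE = 0.0722 × √0.9 = 0.0685; ratio 1.054.

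| ρ (assumed) | SE too large by | Actual type I error | Power without / with country, 0.5 = total SD | Power without / with country, 0.5 = within-country SD |
|---|---|---|---|---|
| 0 | 0% | 5.0% | 79.1% / 79.1% | 79.1% / 79.1% |
| 0.026 | 1.3% | 4.7% | 79.4% / 80.2% | 78.4% / 79.1% |
| 0.05 | 2.6% | 4.4% | 79.7% / 81.1% | 77.6% / 79.1% |
| 0.10 | 5.4% | 3.9% | 80.4% / 83.2% | 76.0% / 79.1% |
| 0.20 | 11.8% | 2.8% | 81.8% / 87.3% | 71.9% / 79.1% |

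**What these shares mean on the outcome scale.** Put the three country means at −g/2, 0 and +g/2, with within-country SD 0.5. The between-country variance is (2/3)(g/2)² = g²/6. For g = 0.2 this is 0.00667. Divided by 0.25 + 0.00667 it gives ρ = 2.6%. Solving backwards, g = √(6 × 0.25 × ρ/(1−ρ)), so shares of 5%, 10% and 20% need gaps of about 0.28, 0.41 and 0.61 z between the extreme countries. These exceed the 0.2 diet effect the trial is sized for.

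**Check by simulation** (4,000 trials per setting, total SD 0.5, ANCOVA with age, sex and baseline). At ρ = 0.10 without country, the mean reported SE was 0.0727 against an empirical SD of 0.068 to 0.069, null rejection was 4.0% and power 79.3%. With country the figures were SE 0.0689, rejection 5.1% and power 82.3%. At ρ = 0.20, null rejection was 2.8% without country and 4.8% with it, and power was 81.8% and 87.4%. These agree with the table within simulation error.

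**The case against.** The strongest reply is that the effect may be close to nil. The model analyses change and also adjusts for baseline, so stable differences in level between countries largely drop out; only differences in how much participants change remain. The article describes common procedures that work against such differences: one energy equation, a standardised interview protocol and a shared visit schedule. No passage shows that countries respond differently. This stands, and it is why the size can only be given as a range starting at zero.

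A reader might infer that the standard errors are too large as a matter of fact, or that power must drop to about 67%. The documents support neither. The 67% figure needs a country share near 30% and the within-country reading of the SD. If 0.5 is the total SD, power without country stays near or above 80% over the range shown, and what is lost is a gain that adjustment would have brought.

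It is also fair that section 2.1 never says stratified or blocked. If the 40:40 split is only a target, or dropout is uneven, balance is inexact and the conservatism shrinks.

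A last reply is that a journal article may leave model detail to the analysis plan. Here, however, the article chose and printed the covariate list, so the question is whether that list is well chosen.

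**Conclusion.** The point holds in conditional form. Allocation is planned as 40:40 within each country, and the published ANCOVA does not use that structure. If country predicts change after age, sex and baseline, the reported standard error is too large, the test runs below its nominal 5%, and power is lower than with country in the model.

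The size depends on an unknown country share. The loss is zero with no country effect and under 1 power point if the extreme countries differ by 0.2 z. At shares of 5% to 20% it is about 1.4 to 5.5 points (total SD) or 1.5 to 7.2 points (within-country SD). These figures assume 96 completers per arm, exact balance within country and the same diet effect in every country.

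It would be wrong to read this as bias or as too many false positives: the estimate stays unbiased and the error is on the conservative side. The omission does not invalidate the planned analysis; it is an efficiency loss that is easily avoided.

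**What to change.** In section 2.9.1, add country (three levels) as a fixed factor to the end-point ANCOVA for the primary outcome and for the other anthropometric and biochemical outcomes. The cost is 2 degrees of freedom out of about 190, which is negligible even if country turns out not to matter. Make the change before any outcome data are seen by arm, so that the added term cannot look data-driven. It would also help to state in section 2.8 whether the SD of 0.5 is within-country or total. A diet-by-country interaction could be reported as an optional supportive check, given the article's claim that three countries aid generalisation, but this point does not depend on it.

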## Figures and Tables

**Figure 1 ijerph-18-04841-f001:**
[figure not shown]
(**a**) Design of the Study. (**b**) Overview of the intervention groups. MD, Mediterranean Diet; MED, Mediterranean; BMI, Body Mass Index; ES, Spain; PT, Portugal; IT, Italy; V, Visit; WC, Waist Circumference.

**Table 1 ijerph-18-04841-t001:** Details on the frequency portions of the Mediterranean basin foods.

Specific Food	Frequency of Portions
Pomegranate	It is recommended at least 2 servings/day of fruit: 14–21 servings/week In addition to the fresh whole fruit, 4 servings of pomegranate juice (200 mL) will be consumed during the week.
Hummus and chickpeas	It is recommended 3 servings/week of pulses (150–200 g (50–80 g dry)). Two servings/week must be cooked chickpeas, minimum one of them as hummus, and another serving may be chickpeas or different pulses. The portion size of hummus is 200 g.
Nuts (almonds, walnuts, and hazelnuts)	It is recommended 3 servings/week: 30 g of mixed nuts/serving. Four servings will be consumed to properly combine the 4 food items included in the MD along the week. Mixed nuts will be walnuts, almonds, and hazelnuts.
Sourdough bread	It is recommended 4–6 servings/day of cereals. Two of these must be a serving of sourdough bread (1 serving of bread is approximately 50–60 g [46,47]).

**Table 2 ijerph-18-04841-t002:** Variables to be analyzed.

Variables	Tool	Timeline
Blood pressure, weight, height, BMI, body composition, WC, WHR	Dietitians/Nutritionists	V1, V2, V3, V4
Physical activity	PAQ-A *	V1, V2, V3, V4
Dietary intake	3-day dietary record *	V1, V2, V3, V4
Food habits	FFQ Helena questionnaire *	V1, V2, V3, V4
MD adherence	KidMed questionnaire *	V1, V2, V3, V4
Quality of life	Kidscreen-27 questionnaire *	V1, V2, V3, V4
Sociodemographic data	HBSC questionnaire *	V1
Knowledge on food and nutrition	NK Helena questionnaire *	V1, V3, V4
Microbiota (feces)	16sRNA sequencing	V1 and V3
Gut-derived metabolites (LPS, SCFAs, lactate, bile acids) (feces and/or plasma)	NMR/GC-MS	V1 and V3
Biomarkers of oxidative stress (8-OHdG, F2-isoprostanes) (urine)	ELISA	V1 and V3
Biomarkers of inflammation (IL-6, CRP, TNFα, MCP1, IL-8) (plasma)	Magnetic bead-based multiplex assays Homeostatic Model Assessment for insulin resistance	V1 and V3 V1 and V3
Biomarkers of adipose tissue function (adiponectin, leptin, resistin) (plasma)		
Biomarkers of insulin resistance (plasma)		
Biomarkers of cardiovascular risk (TMAO) (plasma and urine)	UHPLC‑MS	

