Circulating levels of glucose and blood lipid profile	Enzymatic assays	V1 and V3
Key food intake biomarkers and phenolic metabolites (urine)	Targeted metabolomics (UHPLC‑MS)	V1 and V3
Advanced glycation end products (AGEs) related analyses (plasma or erythrocytes)	ELISA / enzymatic assays	V1 and V3

V: visit; BMI: body mass index; WC: waist circumference; WHR: waist–hip ratio; MD: Mediterranean diet; LPS: lipopolysaccharides; SCFAs: short-chain fatty acids; IL-6: interleukin 6; CRP: C-reactive protein; TNFa: tumor necrosis factor alpha; MCP1: monocyte chemoattractant protein-1; IL-8: interleukin 8; TMAO: trimethylamine N-oxide; PAQ: physical activity questionnaire; FFQ: food frequency questionnaire; HBSC: health behavior in school-aged children; NKQ: nutrition knowledge questionnaire; NMR: nuclear magnetic resonance; GC-MS: gas chromatography coupled to mass spectrometry; ELISA: enzyme-linked immunosorbent assay; UHPLC-GC ultrahigh-pressure liquid chromatography coupled to mass spectrometry. * These variables will be collected through the app.

**Table 3 ijerph-18-04841-t003:** Description of study visits.

Visit	Type of Visit	Description
0	pre-screening visit before randomization	To check inclusion/exclusion criteria in the study
1	after randomization, inclusion visit	Feces, urine, and blood samples will be collected, anthropometric and blood pressure will be measured, and questionnaires (food, knowledge and physical activity) and dietary records will be completed.
2	after 2 months	Anthropometric and blood pressure will be measured, and questionnaires (food, knowledge and physical activity) and dietary records will be completed.
3	after 4 months, final study visit	Feces, urine, and blood samples will be collected, anthropometric and blood pressure will be measured, and questionnaires (food, knowledge and physical activity) and dietary records will be completed.
4	visit 4 months after the end of the intervention	Anthropometric and blood pressure will be measured, and questionnaires (food, knowledge and physical activity) and dietary records will be completed.

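### Within-arm tests of raw weight, height and waist against zero change in 13–17-year-olds can reflect growth rather than diet (secondary results only)

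*Protocol article*

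**What the plan says.** All references are to the protocol article.

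- **Primary outcome (2.7):** "The primary outcome is the BMI z-score, which is a standardized measure of BMI based on specific age and sex". The same section says effectiveness is judged by comparing this score between the two arms.
- **Between-arm analysis (2.9.1):** an ANCOVA of change from baseline in the anthropometric and biochemical parameters, in which "the variables age and sex, as well as baseline values, will be included as covariates".
- **Within-arm analyses (2.9.1):** two follow directly. First, "Within each group (MD and low-fat diet), changes from baseline will also be analyzed at the end point by a paired *t* test". Second, "changes from baseline will also be analyzed considering the different time points using a general linear model for repeated measures". Neither sentence names variables or covariates. The section closes by "setting the level of statistical significance at bilateral 5" per cent for all its tests.
- **Anthropometric variables (2.7):** "Anthropometric data: weight, height, BMI (weight/height^2^), body composition using bioimpedance, waist circumference (WC), and waist–hip ratio (WHR"). Table 2 lists "Blood pressure, weight, height, BMI, body composition, WC, WHR" at visits 1 to 4. No age or sex standardisation is stated for any of these.
- **Timing:** visit 3 is at 4 months. Table 3 describes visit 4 as "visit 4 months after the end of the intervention", which is 8 months from baseline. Section 2.7 gives visit 4 the aim of examining a medium-term impact on anthropometry.

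**The concern.** A within-arm test takes zero mean change as its null. For raw height, weight and waist in 13–17-year-olds, many of whom are probably still growing, zero is not the value to expect without a diet effect. A significant gain in weight may be growth at unchanged BMI, and a significant change in height is essentially growth.

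The plan protects its main comparisons against this: the primary outcome is standardised for age and sex, and growth common to both arms cancels in the ANCOVA. The within-arm tests have no such protection. A paired t test cannot carry age or sex. A general linear model could, but none is stated, and adjusting for age and sex would not remove average growth from the mean change over time. Section 2.1 also rules out an untreated arm, so expected growth cannot be estimated inside the trial.

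At stake is the reading of secondary results. The within-arm model is the only analysis described across the visits, so it stands closest to the visit 4 aim, where growth has had longest to accumulate.

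**Working it through.** **Inputs from the document.** 120 per arm (2.1), 20% dropout (2.8), two-sided 5% (2.9.1). Completers per arm: 120 × 0.8 = 96.

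**The plan's own figure.** With a difference of 0.2, SD 0.5 and 80% power, n = 2 × (1.960 + 0.842)² × 0.5² / 0.2² = 98.1, so 99 per arm. Then 99 × 1.2 = 118.8, so 119 per arm or 238 in total, against the stated 240. This figure concerns the between-arm comparison and plays no part in the point.

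**Assumed inputs (none is in the document).** BMI 30 kg/m², height 165 cm, growth g of 0.3 to 1 cm, SD of weight change 2–4 kg, waist-to-height ratio 0.60, SD of waist change 3–5 cm, SD of height change 0.6–1.5 cm.

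**Method.** Probability of a significant increase in a paired t test with 95 df (critical value 1.985), from the noncentral t distribution with noncentrality = mean change / (SD / √96).

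**Weight at constant BMI.** Added weight = 30 × [(1.65 + g)² − 1.65²], with g in metres. For g = 0.01 this is 30 × (2.7556 − 2.7225) = 0.99 kg. At SD 3 kg the noncentrality is 0.993 / 0.306 = 3.24.

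| Growth | Added weight | SD 2 kg | SD 3 kg | SD 4 kg |
|---|---|---|---|---|
| 0.3 cm | 0.30 kg | 30% | 16% | 11% |
| 0.5 cm | 0.50 kg | 67% | 36% | 22% |
| 1.0 cm | 0.99 kg | >99% | 89% | 67% |

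With no mean change, the probability of a significant gain would be 2.5%.

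**Waist at a constant ratio.** 1 cm of growth adds 0.60 × 1 = 0.6 cm, significant in 49%, 31% and 21% of trials at SD 3, 4 and 5 cm.

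**Height.** 0.5 cm of growth is significant in 98–100% of trials at SD 0.6–1.2 cm, and in 90% at SD 1.5 cm.

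**Growth offsetting a loss.** A true diet effect of −1 kg with +1 kg of growth gives zero mean change, so the weight test rejects in 5% of trials. Without growth it would reject in 90% (SD 3 kg).

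**Between-arm check.** Simulating 20,000 trials with +1 kg in both arms, SD 3 kg and no diet difference, the within-arm test is significant in 90% and the between-arm test in 5.1%.

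**Raw BMI.** Division by height squared already absorbs much of the growth. An assumed drift of 0.1 kg/m² with SD 1.0–1.5 gives 10–16% (both tails). A drift of 0.3 would give 49–83%, but drift over 4 months is expected to be small.

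No separate figure was computed for the repeated-measures model or for 8 months.

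**The case against.** The strongest reply is that no wrong conclusion is planned. Effectiveness is judged between arms on a standardised score, and the within-arm tests are additional. A reader might infer that the trial will claim efficacy from within-arm p-values. Nothing in the document says so, and the visit 4 sentence in 2.7 names no test. This part of the reply stands and keeps the point minor.

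Second, the within-arm sentences name no variables, and the full plan may restrict them. That is fair, but they follow directly on the sentence about anthropometric change, and Table 2 lists raw measures at every visit, so inclusion is the natural reading. BMI z-score is probably also tested within arms, so a standardised result would stand beside the raw ones.

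Third, a reader might infer that raw BMI misleads too, or that the weight test is in error when growth offsets a loss. Neither is supported. Raw BMI is the sensible yardstick in that case: 1 cm of growth at unchanged weight lowers BMI from 30 by 0.36 kg/m², which a paired BMI test would show in 94% of trials at an assumed SD of 1.0. The weight test correctly reports no weight change; only reading that as no diet response would be wrong.

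Fourth, every growth and SD input is assumed, and participants near final height contribute little. This stands, and is why the result is a range.

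Finally, BMI z-score may itself drift without treatment. Section 2.1 cites untreated controls whose percentage overweight rose by 2.1%. Standardising therefore removes the growth problem but does not make a within-arm change a treatment effect, and the fix must say so.

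**Conclusion.** The point holds for the within-arm tests of raw height, weight and waist, as a minor matter of secondary analysis. Growth can make these measures change significantly with no diet effect: in 36–89% of trials for weight, under 0.5–1 cm of growth at constant BMI, a change SD of 3 kg and 96 completers per arm, and in 11% to over 99% across the whole assumed range. Height is the clearest case and waist is weaker.

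These sizes rest on assumptions, including that many participants are still growing, which is inferred from the age range. The stronger reading, that the trial's main result mixes growth with diet, is not supported: the primary BMI z-score comparison and the between-arm ANCOVA are unaffected. Raw BMI is at most slightly affected, provided its drift over 4 months is small.

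**What to change.** In section 2.9.1:

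1. Base within-arm inference on BMI z-score, already the primary measure, and optionally on waist-to-height ratio.
2. Report within-arm change in raw height, weight and waist as mean and SD, without p-values. Raw BMI can stay as planned.
3. State that all within-arm changes, standardised or not, are uncontrolled, and that conclusions on diet effect rest on the between-arm ANCOVA, including those on the medium-term impact on anthropometry at visit 4.

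The cost is slightly more analysis wording and fewer within-arm p-values. Height, weight and waist are already measured at visits 1 to 4, and the BMI z-score already requires a growth reference. Diets, visits, sample size, primary outcome and the ANCOVA model stay as they are.
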